**2.5. Administration of Surveys and/or Process**

All participants will attend a 4-day workshop in prolonged exposure. All participants will all complete self-report measures at various time points: 1) prior to completing the workshop, 2) after completing the workshop, and 3) at 3-month intervals over the course of the 18 months following the completion of training (for standard providers, following the workshop; for extended providers, following their 2 supervised PE training cases). These self-report measures should take approximately 20-30 minutes to complete. Participants who are randomized to Extended PE training condition will additionally be asked to participate in weekly telephone consultation for two PE training cases, which we expect to last approximately 6 months. Patients of the participating providers who consent will be evaluated at two time points: once before they begin treatment (first assessment) and once after receiving 8-15 sessions of treatment, or after 5 months since the initial assessment, whichever comes first (second assessment). Patients who complete or leave the study before receiving 8 sessions of treatment will be asked to complete a second assessment at the time of termination. The consent and first assessment sessions will take a total of 2 to 2.5 hours. The second assessment will take approximately 1 hour. Patients will also be asked to complete self-report measures every 14 days. These measures can take 10-15 minutes to complete.

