**2. Study Instruments**

*2.1. Provider Measures*

Provider Demographics & Background Survey: The Provider Demographics Form assesses standard demographics (ethnicity, gender, age, etc.) and professional information (e.g., military rank, type of schooling, etc.). It also includes items designed to assess providers training, theoretical orientation and experience providing evidence-based treatments, including their knowledge of PE, experience with PE, and attitudes towards PE. This measure will be completed by providers in both conditions.

Provider Measure of Attitudes: This is a 59-item measure of current treatment practices (7 items), beliefs about the effectiveness of PE (1 item), self-confidence in delivering PE (8 items), and perceptions about patient factors that would influence providers decision to use PE (22 items). In addition, this measure includes an embedded, modified version of the 21-item Therapist Beliefs about Exposure Scale (TBES; Deacon et al, 2013). All TBES items were modified to refer to PE specifically, rather than exposure therapy which is a more general term. The TBES has strong psychometric properties including excellent internal consistency ( = .90-.96), high test-retest reliability (r = .89; Deacon et al., 2013). The Provider Measure of Attitudes will be completed by providers in both conditions prior to attending the PE training workshop, after attending the PE training workshop, and at regular 3-month intervals over the course of 18 months following the completion of training (i.e. for providers in the standard condition, after the completion of the training workshop; for providers in the extended condition, after the completion of two supervised PE training cases).

Procedures Used in Treatment Checklist: This 4-item form is meant to collect data on what treatment techniques providers used during their sessions with study patients. Providers will also use the form to record patients’ biweekly PCL and PHQ-9 scores.

*2.2. Patient Measures*

Patient Demographics: The Patient Demographics Form assesses standard demographics (ethnicity, gender, age, etc.).

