**5. Protocol**

*5.1. Abstract*

This study will examine how evidence-based therapies (EBTs), such as Prolonged Exposure (PE) for posttraumatic stress disorder (PTSD) can be successfully disseminated and implemented in the Army by comparing two PE training models: Standard PE training (workshop only) and Extended PE training (workshop plus consultation). Two hundred (200) mental health providers at three medium-to large CONUS Army installations will be randomly assigned to either Standard PE training or Extended PE training. All providers will receive a 4-day PE workshop, along with the distribution of training materials and treatment manuals, conducted at the military site by the Overall Study PI, [name], and her team. Following the 4-day workshop, participants randomized to the Extended PE training will receive weekly phone consultation with a PE expert on two PE therapy cases followed by twice monthly telephone consultation as needed for six months. Participants randomized to the Standard PE training group will not receive any additional consultation following the workshop. Providers will not be required to use PE therapy to treat their patients with PTSD; using PE will be optional. A major outcome of this study is the proportion of the providers PTSD patients that are offered PE. The mental health outcomes of providers PTSD patients will also be monitored as a second major outcome. Patients seeking care for PTSD from participating providers will be recruited, consented and offered treatment for PTSD and related problems to prospectively and systematically assess what type of treatment they are offered and their response to treatment.

*5.2. Objectives*

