**6. Study Design**

**Phase***

Not applicable

*6.1. Design*

This is a randomized clinical trial comparing two methods of training mental health providers in Prolonged Exposure (PE) treatment for Posttraumatic Stress Disorder (PTSD). Two hundred (200) mental health providers at three medium-to-large CONUS Army installations will be randomly assigned to either Standard PE training or Extended PE training. All providers will receive a 4-day PE workshop, along with the distribution of training materials and treatment manuals, conducted at the military site by the Overall Study PI, [name], and her team. Following the 4-day workshop, participants randomized to the Extended PE training will receive weekly phone consultation with a PE expert on two PE therapy clinical cases followed by twice monthly telephone consultation as needed for six months. Participants randomized to the Standard PE training group will not receive any additional consultation following the workshop. Providers will not be required to use PE therapy to treat their patients with PTSD; using PE will be optional. A major outcome of this study is the proportion of the providers PTSD patients that are offered PE. The mental health outcomes of providers PTSD patients will also be monitored as a second major outcome. Patients seeking care for PTSD from participating providers will be recruited, consented and offered treatment for PTSD and related problems to prospectively and systematically assess what type of treatment they are offered and their response to treatment.

*6.2. Study duration*

The study is expected to start in May 2014 and end in May 2017. Subject recruitment and data collection will mostly occur in years 2, 3, and 4. Data analysis will occur in year 4.

*6.3. Resources necessary for human research protection*

Describe research staff and justify that the staff are adequate in number and qualifications to conduct the research. Describe how you will ensure that all staff assisting with the research are adequately informed about the protocol and their research related duties. Describe access to a population that would allow recruitment of the targeted number of subjects. If medical or psychological services as a consequence of the research, describe how the subject will be referred to those services. Describe your facilities and justify that the facilities are adequate. Verify that there is sufficient time to conduct and complete the research.

*6.4. Research Staff*

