**Subjects enrolled by Collaborating Researchers**

120

*7.2. Accrual*

Provider-participants: The On-Site PI will present information about the study and participation to all mental health providers who provide psychotherapy at each site. Those who meet the inclusion and exclusion criteria will be invited to participate in the study and provided informed consent. The project coordinator and research assistant at each site will assist with the coordination of recruitment, screening, and informed consent of participants.

Patient-participants: Patients who screen positive for PTSD according to the PCL-5, PCL-C, or whichever screening measure is used as the performance site’s screening tool for PTS, and who are assigned to one of the provider-participants enrolled in the study will be invited to participate in the study and will meet with a member of the research team to review informed consent. Patients who consent to the study will complete a baseline evaluation with a BOA that includes the CAPS, the M.I.N.I, and self-report questionnaires.

*7.3. Key inclusion criteria*

Key inclusion criteria for provider-participants are the following:

- Male and female mental health providers whose job duties include providing psychotherapy to adult patients, ages 18-65, seeking treatment for PTSD.

- 20% of expected patient caseload with trauma related difficulties

- Support from local leadership to ensure that providers are granted the time and resources necessary to participate in study activities, including providing 90-minute once weekly sessions, time off to participate in the training workshop, time to participate in consultation , time to complete study assessments, etc.

Key inclusion criteria for patient-participants are the following:

- Male and female patients aged 18-65 who are seeking treatment from one of the mental health providers participating in this study.

- Clinically significant PTSD symptoms, defined as a severity score of 25 or greater on the Clinician-Administered PTSD Scale for DSM-5 (CAPS-5).

*7.4. Key exclusion criteria*

Key exclusion criteria for provider- participants are the following:

- Definite plans to terminate their position or relocate from the Army base at some point during the 1 year following training.

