Participants randomized to the Standard PE training group will not receive any additional consultation following the workshop. In addition to mental health providers, patients seeking treatment from participating providers will be recruited and consented to examine their symptoms of PTSD and related problems during treatment. Providers will not be required to use PE therapy to treat their patients with PTSD; rather it will be an option for treatment. A diagnostic feedback form will be given to the provider by the BOA within 24-hours (with more time allotted as needed on a case-by-case basis) of completing both the first and second assessments and will contain a summary of the assessment data. This assessment data may be used by the provider, as he or she deems appropriate, for ongoing treatment decisions. Clinical care of patients enrolled in this study will not be video-taped. Choice of treatment modality will be one of the outcome measures; data on techniques used in treatment will be collected from study providers after every session with a study patient via the Procedures Used in Treatment Checklist. The Checklist will also be used by providers to record their study patients’ self-reported PTS and depression scores, which the providers will acquire from their AHLTA (medical record) session notes on a biweekly basis.

*8.2. Analysis Plan*

The first set of Objectives concern therapist behaviors, specifically hypothesizing that Extended Training will result in a greater proportion of PTSD patients treated with PE, use of PE with more complex patients (e.g. comorbidities). The analyses will be done using mixed effects regression models with repeated measures, incorporating as covariates baseline values on the outcome measures when available and confounded ancillary variables as needed. Planned between and within-group contrasts will be done at each assessment by t-test. The measures to address the first two objectives will be derived from self-report scales completed after consultation. When feasible, summary measures will be derived by summing items bearing on the same issue. For example, the Implementation Survey includes a 25-item section listing comorbid conditions and complicating factors. The fidelity analysis will be based on ratings by IEs of recorded sessions.

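### The 3-monthly provider surveys start at the workshop in the Standard arm but about 6 months later, after two supervised cases, in the Extended arm, so same-named waves are not comparable and non-finishers have no survey date

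*Protocol*

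**What the plan says.** Section 2.5 has all providers complete self-report measures before the workshop, after it, and then "at 3-month intervals over the course of the 18 months following the completion of training". It defines completion of training by arm: "for standard providers, following the workshop; for extended providers, following their 2 supervised PE training cases". Section 2.1 repeats the rule for the Provider Measure of Attitudes; the series starts, "for providers in the extended condition, after the completion of two supervised PE training cases". Section 2.5 gives the expected gap between the two starting points: Extended providers take part in "weekly telephone consultation for two PE training cases, which we expect to last approximately 6 months".

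Section 8.2 then states: "Planned between and within-group contrasts will be done at each assessment by t-test". It takes the measures for the provider objectives from self-report scales filled in after consultation, which Standard providers do not receive. It models attitudes at post-consultation and at two and three years, which does not match the 3-monthly schedule of sections 2.1 and 2.5.

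Sections 5.1 and 6.1 add a second phase of consultation after the two cases, "followed by twice monthly telephone consultation as needed for six months". The procedures in section 8.1 do not mention it. Section 7.4 excludes providers with definite plans to leave their post or "relocate from the Army base at some point during the 1 year following training".

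**The concern.** In a randomised comparison, both groups should be observed at the same time from a common origin, and who is observed should not depend on what happens after randomisation. The 3-monthly series meets neither condition.

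The first problem is time. The protocol itself gives reason to think that elapsed time matters. Section 5.3 cites a trial of motivational interviewing training in which workshop-only providers had lost their early gains by 4 months. Section 8.2 expects attitudes to shift very early in training. A 6-month offset is large on that scale.

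The second problem is who is followed. Attending the workshop starts the Standard clock. Finishing two supervised cases starts the Extended clock, and less engaged providers may never get there. If they are then not surveyed, the comparison sets all Standard providers against a selected part of Extended.

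At stake are the survey-based comparisons of PE use and provider attitudes, which bear on whether consultation is worth its cost.

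**Working it through.** **Inputs.** Nominal waves w = 3, 6, 9, 12, 15, 18 months (section 2.5). Expected length of the two supervised cases L = 6 months (section 2.5); a range of 3 to 9 months is assumed to show sensitivity. The protocol states no power or error-rate figure that depends on this point, so there is nothing to reproduce first.

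**Step 1, time since workshop.** Standard: t = w. Extended: t = L + w.

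| Nominal wave | 3 | 6 | 9 | 12 | 15 | 18 |
|---|---|---|---|---|---|---|
| Standard | 3 | 6 | 9 | 12 | 15 | 18 |
| Extended, L = 6 | 9 | 12 | 15 | 18 | 21 | 24 |
| Extended, L = 3 | 6 | 9 | 12 | 15 | 18 | 21 |
| Extended, L = 9 | 12 | 15 | 18 | 21 | 24 | 27 |

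With L = 6, every same-named wave is 6 months apart.

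**Step 2, what re-indexing could recover.** With L = 6, both arms have surveys at months 9, 12, 15 and 18 after the workshop, that is 4 of 6 waves per arm, under different nominal labels. Extended has no wave of the series at months 3 and 6. Recovery depends on L: with L = 4, Extended waves fall at 7, 10, 13, 16, 19 and 22 months and none coincides with a Standard wave.

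**Step 3, overlap with consultation.** If the twice-monthly phase applies, Extended consultation can run to L + 6 = 12 months after the workshop. With L = 6, nominal waves 3 and 6 (months 9 and 12) then fall during it or at its end.

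**Step 4, non-finishers.** The Extended start is defined only for providers who complete two cases. Sections 2.1 and 2.5 give no other start, and no other section supplies one.

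**Step 5, illustrations with no true effect (assumed inputs, not estimates).** Providers per arm: n = 100 (section 2.4), or 60 if the total of 120 in the protocol description is split equally (assumed). Two-sided 5% normal test, outcome in SD units. False-positive rate = Φ(b/se − 1.96) + Φ(−b/se − 1.96).

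- *Timing.* Let b be the drift over 6 months and se = √(2/n). For b = 0.1, n = 60: se = 0.183, b/se = 0.548, rate 8.5%. For b = 0.2, n = 60: 19.5%. For n = 100: 10.9% and 29.3%.
- *Selection.* Let a fraction c of Extended finish, and let finishing correlate ρ with the outcome. Then b = ρ·φ(z)/c with z = Φ⁻¹(1 − c), and se = √(1/n + 1/(cn)). For c = 0.9, ρ = 0.2: b = 0.04 SD, rate 5.5% (n = 60) or 5.8% (n = 100). For c = 0.6, ρ = 0.4: b = 0.26 SD, rate 23.1% or 35.1%.

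These show only that moderate drift or selection would matter at these sample sizes. The protocol gives neither drift, completion rate nor correlation.

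**The case against.** The strongest defence is that counting from the end of assigned training is deliberate. It compares providers at equal time after each programme is finished, and it keeps the supervised training cases, which are PE by design, from inflating Extended's reported use. That concern is legitimate, and the fix must deal with it. But the stated question is whether adding consultation to a workshop increases PE use, and a like-for-like randomised answer needs a common origin.

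A second defence is that a statistical analysis plan, not shown here, could re-index by time since workshop. With a 6-month offset this would work for months 9 to 18. It could not create the missing early Extended waves or give non-finishers a start date.

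Several stronger readings are tempting, and the documents do not support them:

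- *Extended non-finishers are dropped.* No section says so. Section 2.5 has all participants completing the measures; the schedule for non-finishers is undefined. Loss is a risk, not a rule.
- *All provider outcomes are affected.* Treatment choice is also recorded after every session on the Procedures Used in Treatment Checklist (section 8.1), which does not use this clock. Neither do the patient assessments. The pre- and post-workshop surveys are aligned.
- *Extended must lose more late waves because eligibility covers one year.* Section 7.4 counts the year from training, and sections 2.1 and 2.5 define completion of training by arm. Read that way, each arm has the same number of waves inside the year.
- *Extended follow-up cannot fit the calendar.* Section 6.2 says: "The study is expected to start in May 2014 and end in May 2017". That is three years, yet the same section places analysis in year 4 and section 6.6 reports four years of funding. The end date is itself inconsistent and cannot carry the argument.

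**Conclusion.** The point stands for the 3-monthly provider series. The arm-specific starting points are stated outright, and the 6-month offset follows from the protocol's own expected duration: 3 to 18 months after the workshop in Standard against about 9 to 24 in Extended. With contrasts planned at each assessment, training model and elapsed time are mixed at every same-named wave. The Extended series also hangs on a post-randomisation event with no date for those who never reach it, which creates a risk of comparing all Standard providers with Extended finishers only.

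The direction and size of the bias cannot be computed from the documents. Decay after the workshop would count against Extended; growth in use, or silent loss of non-finishers, would count in its favour. A reader should not infer that the result is biased by a known amount or towards a known arm. The matter should be settled before the surveys begin, because waves not collected cannot be recovered in analysis.

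**What to change.** Anchor the 3-monthly surveys in both arms to one date, either randomisation or the end of the workshop, at months 3, 6, 9, 12, 15 and 18. Survey every randomised provider on those dates, whether or not the two cases are finished, and analyse as randomised. Base the main between-arm contrast on a common-date wave after Extended consultation has ended. If the twice-monthly phase applies, that end is at about 6 + 6 = 12 months, so month 15 or 18 serves better than month 12; if the cases took 9 months (assumed), it would be 9 + 6 = 15, which favours month 18. Report PE use in the supervised training cases separately from use with other patients. Time since consultation ended can remain a descriptive, Extended-only analysis.

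The cost is a protocol amendment and a new survey calendar, with no extra surveys. Three downsides should be accepted openly. Early common-date Extended waves fall during consultation. A main wave at month 15 or 18 lies beyond the 1-year stay that eligibility screens for, so some providers will be lost and the plan should say how they are handled. Extended follow-up would end at month 18 rather than about month 24, that is about 18 − 6 = 12 months after the two cases.

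Separately, three sets of text need reconciling: the assessment times in sections 2.1, 2.5 and 8.2; the twice-monthly consultation present in sections 5.1 and 6.1 and absent from 8.1; and the study end date in section 6.2 against the year-4 activities there and the four-year funding in 6.6.

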**2.6. Data Management**

Research files will be created for each study participant (provider and treatment-seeking PTSD patients). All data collection sheets will be coded. Research staff at each of the performance sites will assign a unique alphanumeric number to each participant and maintain the link between PHI and the code only at the local site. Research files will be maintained in a locked filing cabinet in a locked office that only study staff can access. From the data collection sheets, all coded research data will be entered into the study database that will be maintained by the University of Texas Health Science Center at San Antonio (UTHSCSA) using the same policies and procedures established for the South Texas Research Organizational Network Guiding Studies on Trauma and Resilience (STRONG STAR) PTSD Research Consortium. Access to the coded research data maintained by UTHSCSA will require a password protected login available only to authorized Biostatistics and Data Management Core staff. Data will be stored in a password-protected centralized database server on a Windows 2003 platform using Microsoft SQL 2005.

**2.7. Medical Information Disclosure***

*Does the research proposal involve the use and disclosure of research subject's medical information for research purposes?*

Yes

**If the answer is YES, indicate which items is provided with this submission:**

Modified research informed consent document that incorporates HIPAA requirements

**Primary Focus***

Sociobehavioral (i.e. observational or interventional)

**Protocol Interventions**

- Sociobehavioral (i.e. cognitive or behavioral therapy)

- Survey instrument

